## **1 Abbreviations**

**AUT:** Online self-help program with automated support

**IND:** Online self-help program with individual support

**TAU:** Treatment as usual control condition (conventional treatment under conditions of routine care); in this case written information material for relatives of persons with depression

### **2.2 Funding**

Financing for this trial has been secured by a grant from the “Innovationsfonds zur Förderung von Versorgungsforschung (§ 92a Abs. 2 Satz 1 SGB V)” with the reference 01VSF19054.

## **3 Introduction**

### **3.1 Background and rationale**

Depressive disorders are among the most common mental disorders globally, and are ranked by the WHO as the single largest contributor to global disability (World Health Organization, 2017). In Germany, 4.9 million adults are estimated to suffer from unipolar depression annually (Jacobi et al., 2014). During the course of their lives, a majority of Germans are affected by depression either directly (23%) or indirectly as relatives or close friends (37%, Deutsche Depressionshilfe, 2018). Depressive

disorders are a leading cause of burden of disease (years lived with disability), both globally and especially in developed countries like Germany (Vos et al., 2012). Societal costs are also very high, with an estimated 210,000 work years lost annually in Germany (Robert Koch-Institut, 2018). Direct treatment costs in Germany are estimated at 4.6 billion Euro per year (König, Luppä, & Riedel-Heller, 2010), most of which is attributable to inpatient treatment and medication. Apart from pharmacotherapy, psychotherapeutic treatments are considered first-line treatments for depressive disorders (Meister et al., 2018) as recognized in national guidelines (DGPPN, BÄK, KBV, & AWMF (Hrsg.) für die Leitliniengruppe Unipolare Depression, 2015).

Relatives, significant others and other caregivers of depressed persons are a group mostly neglected by current health care systems, despite the fact that they face increased pressures on in the form of objective and subjective burdens and caring responsibilities for the patients as a result of deinstitutionalization of mental health services (Franz, Meyer, & Gallhofer, 2003). Depression puts a great strain on partnership and family: 84 percent of those affected withdraw from social relationships during a depression, according to a recent representative survey by the German Foundation for Depression (Deutsche Depressionshilfe, 2018). Half of those affected by depression experience problems in their partnership, and in 45 percent of these cases the couple ends up separated. The depressive disorder is associated with considerable subjective and objective stress, even for healthy relatives and partners (Bischkopf, Wittmund, & Angermeyer, 2002; Franz et al., 2003): the vast majority of relatives and partners are concerned about the health (95%) and future (86%) of the depressed person, as well as their own future (66%; Franz et al., 2003). The majority suffers from negative feelings such as guilt, shame or fear of the future and experience physical and psychosomatic complaints. (Frank, Hasenmüller, et al., 2015; Franz et al., 2003). As a result, the relatives' ability to cope with everyday life, their relationships and leisure activities are often impaired. These strains also manifest in the caregivers' risk of developing a depressive disorder themselves. The 1-year prevalence of depression is found to be more than doubled among caregivers of depressed individuals in comparison to the general population (Butterworth & Rodgers, 2006; Ildstad, Ask, & Tambs, 2010; Wittmund, Wilms, Mory, & Angermeyer, 2002). An international review (Steele, Maruyama, & Galynker, 2010) has shown that relatives of people with bipolar disorder, where depressive episodes usually predominate, have

significantly higher rates of depression and other mental illnesses, combined with an increased health care utilization. Reducing this risk should be a central goal of health policy, because a first depressive episode is followed by a recurrent depressive disorder in at least 50% of cases, and thus leads to further episodes, with the aforementioned consequences for those affected and for society. Also, there is evidence suggesting an interaction between the stress experienced by relatives and the course of depression in the patients. A greater burden on relatives significantly increases the risk of recurrences and chronic courses of the disease (Hölzel, Härter, Reese, & Kriston, 2011; Perlick, Rosenheck, Clarkin, Raue, & Sirey, 2001).

Almost one in three relatives say that they are poorly informed about depression (Deutsche Depressionshilfe, 2018). However, lack of knowledge among relatives results in less understanding for the patient, less support and misinterpretation of depressive symptoms such as social withdrawal and reduced emotions. On the other hand, a review (Jacob & Bengel, 2000) concluded that specific information for patients and relatives about the disease depression lead to a better understanding of the disease and a higher treatment satisfaction on the part of the patient. Psychoeducational offers for relatives, which include problem-solving and coping strategies in addition to pure knowledge transfer, can reduce the objective and subjective burden on relatives (Katsuki et al., 2011; Shimazu et al., 2011). After the intervention, the percentage of the relatives showing signs of anxiety and depression could be reduced from 50% to 9%. There is also evidence suggesting that recurrence of depression has been reduced after the relatives' participation in psychoeducational courses (Shimazu et al., 2011): The authors report the recurrence rate at 9-month follow-up to be only 9% in the psychoeducation group compared to 50% in the randomized treatment-as-usual control group. In line with this, a more recent paper reviewing 10 studies on psychoeducation for relatives of depressed individuals showed predominantly positive results both in terms of the relatives' strain and the depressive symptoms of the affected (Brady, Kangas, & McGill, 2017). A multi-center study (SCHILD) on group psychoeducation relatives of persons in inpatient depression treatment has just been completed in Germany, but the results are not published yet (Frank, Wilk, et al., 2015).

The importance of psychoeducation for relatives is also underlined by a recommendation in the current S3 guidelines/NVL "Unipolar Depression" (DGPPN et al., 2015). Despite the importance of such services for relatives, there is a dramatic

undersupply. In a survey of all psychiatric hospitals in Germany, Austria and Switzerland, only about 70% of the hospitals stated that they offered psychoeducation courses for relatives of depressive patients at all (Rummel-Kluge, Kluge, & Kissling, 2015). Moreover, only 13% of the relatives in these clinics took part in these offers. The authors discussed possible reasons for this and mentioned inflexible times of the offers, far travel to reach the clinic, and the fear of stigmatization associated with a visit to the clinic. Frank and colleagues (2014) reported similar results from a survey of German acute care hospitals: Only one in three clinics offered groups for relatives of depressive patients, and only one in five relatives participated in these groups (Frank et al., 2014). Hence, only about 5-10% of relatives of depressive patients undergoing inpatient treatment are reached.

In the outpatient setting, the situation of relatives of depressive patients is even worse, as offers for relatives are not included in psychotherapy guidelines. While psychiatric specialist can provide services to relatives that are reimbursed by German public health insurances, this option is hardly used due to organizational obstacles. As only 21% of the first-depressive patients receive an inpatient treatment (Gerste & Roick, 2014), the vast majority of relatives of depressive patients do not have access to psychoeducational services provided by specialists in routine care. Due to this problematic supply situation, self-help-offers are an important additional resource for patients as well as relatives. In this area, digital services have become increasingly important throughout Germany and internationally (Deutsche Depressionshilfe, 2017). For these reasons, an online self-help program for relatives and close friends of persons with depression was developed ([www.familiencoach-depression.de](http://www.familiencoach-depression.de)). The program was developed based on the current scientific literature by [name] working group at the University of Freiburg Medical Center in cooperation with the German AOK health insurances federal association, with the help of an expert advisory council, and with the involvement of focus groups of depressed individuals and relatives of depressed persons. The program is available freely and free of charge since 9/2018. It is met with great interest and acceptance among users as well as experts (a reference will be included in the new S3 guidelines for unipolar depression). However, the family coach depression is only available as an unaccompanied online program so far.

The efficacy of online-interventions in the prevention of mental disorders is evaluated positively in a recent review of meta-analyses (Ebert et al., 2018), even

though the authors note a comparatively small number of studies. Purely informative online-interventions are found to be significantly less effective than guided interventions (Baumeister et al., 2014). At the same time, it is unclear if therapeutic guidance by highly qualified coaches is more effective than purely practical and motivational guidance (Andersson & Titov, 2014). Attempts to automate human guidance, which would help to economically disseminate preventive interventions to a broad public, are still in their infancy (Kelders, Bohlmeijer, Pots, & van Gemert-Pijnen, 2015). Therefore, in the context of the present study we aimed to develop and evaluate both an individualized message system with support provided by trained psychologists, as well as an automated message system aimed at keeping the users motivated and engaged and thus increase the effectiveness of the measure.

### **3.2 Objectives and estimand**

The objective of the research project is to increase the efficacy of an online self-help program for caregivers of depressed persons by developing and implementing individualized vs automated support via secure e-mail messages. Within this evaluation study the following primary research question will be addressed: Which impact has the four-week usage of the online self-help program with individualized or automated e-mail support vs treatment as usual on the risk of mental diseases in caregivers? In order to achieve this, we strive to determine if a treatment policy assigning caregivers of depressed persons to an individualised or automated online self-help intervention reduces the caregiver's unspecific mental distress compared to assignment to treatment as usual (TAU), as measured by the change of the K-10 score from baseline to four weeks after randomisation (post-measurement minus baseline). The change in mental distress is considered relevant regardless of whether or not the caregiver adheres to or discontinues the assigned treatment. Treatment arms should be compared with respect to the difference in means of the change in K-10 score.

---

 The self-help program evaluated in this study addresses relatives as well as close friends, colleagues, roommates etc., who give support to a depressed person and are affected by the depressive disorder. In the following, they will be referred to summarily as caregivers.

### 3.3 Hypothesis

**Primary hypotheses:** The online self-help program with individualized (IND) or automated (AUT) e-mail support reduces the unspecific mental distress of the caregivers (as an indicator for the risk of mental diseases) as compared to TAU. In a comparison of the two kinds of support, the individualized support will be more effective than the automated support.

**Secondary hypotheses and goals:**

- The online self-help program with individualized or automated e-mail support reduces the psychosocial burden and the subjective symptom burden of the caregivers as well as the depressive symptoms in the depressed person. It improves depression literacy, interaction behaviour and the well-being of the caregivers.
- Assessing the acceptance and usage of the online self-help program
- Identification of moderators and mediator variables
- Qualitative evaluation of (a) the caregivers' experiences with the online self-help program, the support conditions, everyday life experiences and the interaction with the depressed person as well as potential changes brought about by the intervention, and (b) the depressed persons' experiences of potential changes in the caregivers behavior and their interactions.

### 3.4 Trial design

The study trial is designed as a randomized, controlled open-label superiority trial with three parallel groups. The randomization will be performed as block randomization with a 2:2:1 allocation (IND:AUT:TAU).

## 4 Methods: Participants, interventions and outcomes

### 4.1 Study setting

The study takes place only on the internet platform ([www.gemeinsam-durch-die-depression.de](http://www.gemeinsam-durch-die-depression.de)). There will be neither additional phone contact nor face-to-face contact. The study is addressed to German-speaking participants in Germany. After registration on the online platform, the online intervention and the messaging system are available in the protected login area of the website.

## **4.2 Eligibility criteria**

### **4.2.1 Criteria for participation of caregivers**

Caregivers can participate in the trial alone or together with their depressed relative, significant other or close friend. If only the caregiver participates in the study, the participant has to provide information on themselves and the depressed person they care for, and both must meet the following in- and exclusion criteria:

#### **Inclusion criteria concerning caregiver:**

- age 18 years and older
- sufficient German language skills
- e-mail account and access to the internet
- informed consent
- caring for a depressed person, who
  - is of age 18 years or older
  - has a primary diagnosis of unipolar depressive disorder OR primarily depressive symptoms (according to caregiver)
  - has no primary diagnosis of any other mental disorder (e. g., bipolar disorder, schizophrenia).

#### **Exclusion criteria concerning caregiver:**

- suffering from any mental disorder

### **4.2.2 Criteria for participation of depressed person**

Additionally, the depressed person can participate in the study to provide direct information on their symptoms, but only together with the caregiver. In that case, the depressed person has to provide information on and meet the following criteria:

#### **Inclusion criteria concerning depressed person:**

- sufficient German language skills
- e-mail account and access to the internet
- separate informed consent

## **4.3 Interventions**

Only the caregiver will receive one of the three interventions. If the depressed person participates as well, he/she only fills in a short questionnaire at each measurement point (and is able to provide additional feedback on the study if desired).

The online self-help program consists of four interactive, independently usable modules (Figure 1). It instructs caregivers on how to deal with common depressive

symptoms (module „Depression und Alltag“). Furthermore, it informs about depression as a mental illness, specific treatment options, critical situations and suicidal tendencies (module „Was muss ich wissen?“) and advises on how to strengthen the relationship between the depressed person and the caregiver (module „Beziehung stärken“). It provides instructions and exercises on how to find the right balance between caring for the depressed person and self-care (module „Selbstfürsorge“). Completing each module will take approximately 1.5 to 2.5 hours per module including homework exercises.

Fig. 1 Structure and modules of the online self-help program

[figure not shown]

During the study period of four weeks, the online self-help program will be offered in the following three individually randomized variants:

1) *Online self-help program with individual support*: The individual e-mail-support will be implemented by specifically trained psychologists and under regular supervision

with experienced psychotherapists. The psychologist contacts the caregivers three times per week via a secure message system, to give additional information about the modules (e.g. using examples), clarify individual content-related questions and strengthen the motivation of the caregivers in dealing with individual obstacles. For the supporting psychologists, guidelines with instructions and text templates will be developed, to reduce the expenditures of time and costs substantially. Because of its high degree of standardisation, the email-support is much more efficient than other possible formats (e.g. telephone or chat). Since many questions will arise repetitively, text templates will be created gradually, which will reduce personnel costs for the individual support.

2) *Online self-help program with automated support:* The fully automated message system includes regular motivational e-mails, reminders with encouraging messages, and feedback on completed modules. In the development of the automated support system, a focus group consisting of experts in e-mental-health and psychoeducation for relatives was conducted, and caregiver experiences were collected in qualitative interviews in a pilot study.

3) *treatment as usual (TAU) control condition with written information:* In the TAU control condition the caregivers receive a digital version of the patient information leaflet „Depression – Angehörige und Freunde“, which was developed by the ÄZQ based on patient guidelines of unipolar depression. (Ärztliches Zentrum für Qualität in der Medizin (ÄZQ), 2016). On two pages, this document presents concise information on living with the situation, supporting the depressed person, managing crises and caring for oneself. After the study period of three months, the caregivers of the TAU control condition can also use the online self-help program with automated support.

## 4.4 Outcomes

### Primary outcome:

The primary outcome of the study is the unspecific psychological distress as indicator for the risk of mental illness in caregivers (K-10-scale) at post-intervention (T2).

### Secondary outcomes:

All outcomes are to be assessed at post-intervention (T2) and at 3-month follow-up (T3)

- The subjective und objective psychosocial burden of caregiving (involvement evaluation questionnaire / IEQ-EU)
- The subjective symptom burden (symptom checklist short version / SCL-K-9)
- The depression literacy (depression literacy test; D-Lit)
- High expressed emotion aspects “critical comments” and “over-involvement” (Familienfragebogen; FFB)
- The well-being (WHO-5) of the caregivers
- Depressive symptoms in the depressed person (patient health questionnaire PHQ-9).

## 4.5 Participant timeline

Before registration on the website, interested caregivers are provided with written information on the study and an e-mail-address of the study team to answer any remaining questions. Informed consent is obtained from participants by actively selecting a checkbox at the end of the informed consent and data protection summary. Afterwards, caregivers can register on the website by filling in their e-mail-address and responding to a verification e-mail (double opt in). Afterwards, the caregiver will be asked some questions to check the in- and exclusion criteria (Screening). If the caregiver fulfills the criteria, he/she will be included in the study and asked, if the depressed person would like to participate as well. At the caregiver's request, a personalized invitation e-mail is sent to the depressed person, which directs him/her to a study information and informed consent page tailored at depressed participants. Then the caregiver (and if applicable the depressed person) will be asked to complete the pre-intervention questionnaires (T0). After completing his/her questionnaires, the caregiver will be randomized (IND:AUT:TAU; 2:2:1) to one of the three interventions:

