### **5.1.2 Allocation concealment mechanism**

The allocation sequence is implemented in the designated online platform. The result of randomization is communicated to the caregivers via internet after informed consent, screening, and entry of their baseline data. Randomization lists are only accessible to the technical administrators of the online platform.

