### **5.1.3 Implementation**

Randomization lists per stratum are generated by IMBI staff not involved in the trial using R version 4.0.2 or higher and supplied to the technical administrators of the online platform. Participating caregivers enroll themselves into the trial during the online informed consent process and are automatically allocated online to one of the three arms using the caregiver's baseline data for stratification.

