## **6 Methods: Data collection, management and analysis**

### **6.1 Data collection methods**

#### **6.1.1 General Data**

By registration on the website the caregiver needs to fill in his/her e-mail-address and user name. Afterwards the caregiver will be asked some questions to check the in- and exclusion criteria (Screening). If the caregiver fulfils the criteria, he/she will be included in the study and asked, if the depressed person would like to participate as well. Then the caregiver will be asked for some general data including sociodemographic data of the caregiver and the depressed person, internet literacy, prior experience with psychoeducation as well as diagnostic and treatment status of the depressed person.

Before the intervention period starts the participant has to fill in the psychological questionnaires at T0 (see 0). If the depressed person participates as well, he/she will be asked to fill in a short questionnaire concerning his/her depressive symptoms. One week after starting the intervention (T1) the caregivers will be asked to fill in a short questionnaire concerning the psychological distress of the caregivers (K-10). After the intervention period of four weeks the caregivers and depressed persons fill in the psychological questionnaires again (T2). At this time there will be an additional questionnaire for caregivers asking for the acceptance, adherence and usage of the online program. All caregivers were also asked, if adverse events were occurring during the intervention period. Three months after T0 (T3) the caregivers and depressed persons will fill in the psychological questionnaires again und the caregivers will be asked for occurred adverse events in the last 8 weeks.

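### Section 4.5 randomises the caregiver on the caregiver's own T0 data, and nothing secures that an invited depressed person's consent and baseline PHQ-9 come before allocation

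*Protocol*

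**What the plan says.** The depressed person enters by a route of their own. Under section 4.5, if the caregiver asks for it, "a personalized invitation e-mail is sent to the depressed person", leading to a separate information and consent page. Section 4.2.2 lists "separate informed consent" among that person's inclusion criteria.

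Section 4.5 then describes T0 for both persons: "and if applicable the depressed person) will be asked to complete the pre-intervention questionnaires (T0". The next step concerns one person only: "After completing his/her questionnaires, the caregiver will be randomized".

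The allocation sections match that trigger. Section 5.1.2: "The result of randomization is communicated to the caregivers via internet after informed consent, screening, and entry of their baseline data". Section 5.1.3 adds that caregivers are "automatically allocated online to one of the three arms" and that the caregiver's baseline data supply the strata.

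On data collection, section 6.1.1 says: "Before the intervention period starts the participant has to fill in the psychological questionnaires at T0". It continues: "If the depressed person participates as well, he/she will be asked to fill in a short questionnaire concerning his/her depressive symptoms". The schedule table in section 6.1.2 places the depressed person's consent under Screening and the PHQ-9 under T0, T2 and T3.

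**The concern.** A person who receives an e-mail invitation has to open it, read the information, consent and complete a questionnaire, and may take days to do so. The caregiver can finish T0 in the meantime and be allocated. The trial is open-label (section 5.2), so the caregiver then knows the arm while the depressed person is still deciding.

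Two things could follow. First, whether a late responder joins may depend on the arm, for example through how much the caregiver encourages it. Section 6.1.4 describes reminders for T1, T2 and T3 and a voucher for caregivers, but no T0 prompt to an invited person who has not replied. For late joiners the comparison would no longer rest on randomisation. Second, a T0 PHQ-9 given after allocation may already reflect the intervention.

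At stake is the only questionnaire outcome measured in the depressed person. It carries a secondary hypothesis in section 3.3, that the program reduces that person's depressive symptoms.

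**Working it through.** The protocol gives no figure for how many depressed persons take part, how many reply late, or by how long. There is thus no figure of the plan to reproduce, and the check is mainly one of sequence.

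**Step 1. What must be complete before allocation?**
- Caregiver: consent, screening and T0 data (sections 4.5, 5.1.2, 5.1.3).
- Depressed person: no condition is stated in any of these sections.

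**Step 2. Does another rule secure the order for the depressed person?**
- Section 4.5 calls T0 pre-intervention, and the section 6.1.2 table shows consent at Screening and PHQ-9 at T0. Both show the intended order. Neither says what happens if the invited person has not replied when the caregiver finishes.
- The rule in section 6.1.1 that T0 precedes the intervention is worded for the participant. The sentence on the depressed person that follows gives no order relative to randomisation.
- Section 8.1 requires consent before trial-specific tests. That is still met if consent and PHQ-9 both follow allocation.
- No section gives the invitation a deadline or excludes a person who joins after allocation.

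So the schedule intends one order, while the stated trigger allows another.

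**Step 3. How far could a late T0 overlap with the intervention?** The PHQ-9 covers the previous 2 weeks (section 6.1.2). Assuming a form completed 7 days after allocation, 7/14 = 50% of its window lies after allocation. This describes the recall window and is not a measure of bias.

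**Step 4. Illustration: late baseline used as a covariate.** Let f be the share of active-arm T0 values taken late, g the share of the effect already present in them, and b the slope on baseline. The active arm's mean baseline shifts by f × g × effect, and adjustment removes b × f × g of the effect. With b = 0.5 (assumed):
- f = 0.1, g = 0.1: 0.5 × 0.1 × 0.1 = 0.005, or 0.5%
- f = 0.3, g = 0.25: 0.5 × 0.3 × 0.25 = 0.0375, or 3.75%
- f = 0.5, g = 0.5: 0.5 × 0.5 × 0.5 = 0.125, or 12.5%

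**Step 5. Illustration: late joining that depends on prognosis in the active arms only.** All inputs are assumed: no true effect, outcome SD 1, baseline-outcome correlation 0.5, uptake 40%. Among the share f of invited persons who decide after allocation, the log-odds of joining fall by γ per SD of worse outcome in the active arms and do not depend on outcome in TAU. The baseline-adjusted spurious difference is approximately −f × γ × (1 − 0.4) × (1 − 0.5²) = −f × γ × 0.6 × 0.75. A simulation under the same assumptions agrees:

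| f | γ | Formula | Simulation |
|---|---|---|---|
| 0.1 | 0.2 | −0.009 | −0.007 |
| 0.1 | 0.5 | −0.0225 | −0.022 |
| 0.3 | 0.2 | −0.027 | −0.031 |
| 0.3 | 0.5 | −0.0675 | −0.065 |
| 0.5 | 0.2 | −0.045 | −0.044 |
| 0.5 | 0.5 | −0.1125 | −0.108 |

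The sign comes from the assumption that those likely to do better join more readily; the opposite assumption reverses it.

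**The case against.** The strongest reply is that the protocol already states the right order: invitation, consent page, T0 for both, then randomisation, with the schedule table to match. On this view only an enforcement rule is missing. The description of the intent is correct. But the sentence that triggers allocation names the caregiver's forms alone, and the two allocation sections repeat that condition. Following the text as written therefore permits late entry.

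Several stronger readings are tempting, and the protocol does not support them:
- A reader might infer that the platform certainly does not wait and shows the arm at once. Section 5.1.2 says only that the result is communicated online after the caregiver's data are entered, and section 5.1.1 says that details of the randomisation algorithm are documented separately. A hold is not described, but neither is it ruled out.
- A reader might infer that caregivers choose whom to invite in the light of the arm. In section 4.5 the request for an invitation comes before T0 and allocation, so only the invited person's response can depend on the arm. That TAU caregivers would encourage less is plausible but not documented.
- A reader might infer that adjustment for late T0 values necessarily removes part of the effect. Section 6.3.5 carries over the covariates of the primary model, and section 6.3.2 names baseline K-10 among them. Use of baseline PHQ-9 is not stated. If it is not used, this mechanism falls away and only the selection mechanism remains.

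It is also fair that the definition of the PHQ-9 analysis set can be left to the SAP, which is not at hand. The order of enrolment, however, is trial conduct fixed in section 4.5. An SAP can exclude late entrants but cannot supply the pre-allocation baseline they never gave.

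**Conclusion.** The point holds as a gap between the intended and the secured order. The written procedure allows an invited depressed person's consent and T0 PHQ-9 to follow the caregiver's open-label allocation. Bias in the PHQ-9 comparison is possible but not shown. It requires that late entry occurs and that it differs by arm or, if baseline PHQ-9 is a covariate, that late values already carry some effect.

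Size and direction cannot be derived from the protocol. Under the assumed inputs, attenuation runs from 0.5% to 12.5% and the spurious difference from about 0.01 to 0.11 SD. The upper ends need half of the baselines or responses to be late.

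The reach is narrow. The PHQ-9 is one of six listed secondary outcomes (section 4.4), and section 6.3.1 confines confirmatory testing to the primary outcome. The K-10 and the other caregiver outcomes have a baseline taken before randomisation and are unaffected, as are the sample size and the test sequence. The change is worth making because it is cheap.

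**What to change.** State in section 4.5 that the depressed person's consent and T0 PHQ-9 must be complete before the caregiver is randomised, that the entry link closes at randomisation, and that the caregiver is told so before submitting T0.

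For persons already enrolled, base the main PHQ-9 analysis on those whose consent and T0 PHQ-9 timestamps both precede the caregiver's randomisation, and show all participants as a sensitivity analysis. Membership of that main set is settled before allocation, so entry into it cannot depend on the arm.

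The cost is a platform setting, a sentence in the protocol, a line in the SAP and somewhat fewer depressed persons in the PHQ-9 analysis. Making the platform wait for the invited person is an alternative, but a debatable one: it could delay caregiver entry, and with it the primary endpoint, for the sake of a secondary outcome.
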